**Administrative, behavioral, and clinical**													
	Locator information	✓		✓		✓		✓		✓		✓	
	HIV counseling	✓		✓		✓		✓		✓		✓	
	Reproductive counseling	✓^a^		✓^a^		✓^a^		✓^a^		✓^a^		✓^a^	
	Condom, lubricant, and HIVST^b^	✓		✓		✓		✓		✓		✓	
	Adherence counseling	✓		✓		✓		✓		✓		✓	
	HIV Risk and Mental health assessment	✓		✓		✓		✓		✓		✓	
	Medical history	✓		✓		✓		✓		✓		✓	
	Concomitant medication	✓		✓		✓		✓		✓		✓	
	Directed physical examination	✓		✓		✓		✓		✓		✓	
	Weight and vital Signs	✓		✓		✓		✓		✓		✓	
	Height											✓	
	HIVST report	✓		✓		✓		✓		✓		✓	
**Laboratory**													
	Third-generation HIV rapid test	✓		✓		✓		✓		✓		✓	
	HIV RNA PCR^c^ (GeneXpert)											✓	
	HBV^d^ rapid test					✓						✓	
	HCV^e^ rapid test					✓						✓	
	Syphilis test^f^	✓				✓				✓		✓	
	Liver function test (ALT^g^)					✓						✓	
	Urine CT^h^ and NG^i^ test	✓				✓				✓		✓	
	Oropharyngeal CT and NG test	✓				✓				✓		✓	
	Rectal swab CT and NG test	✓				✓				✓		✓	
	Urine pregnancy test	✓^a^		✓^a^		✓^a^		✓^a^		✓^a^		✓^a^	
	Plasma and Serum storage	✓		✓		✓		✓		✓		✓	
**Study medication**													
	Injection	✓		✓		✓		✓		✓		✓	
	ISR^j^ evaluation	✓		✓		✓		✓		✓		✓	

^a^Only for transgender men.

^b^HIVST: HIV self-testing.

^c^PCR: polymerase chain reaction.

^d^HBV: hepatitis B.

^e^HCV: hepatitis C.

^f^Rapid test plus nontreponemal syphilis testing, as indicated.

^g^ALT: alanine aminotransferase.

^h^CT: *Chlamydia trachomatis*.

^i^NG: *Neisseria gonorrhea*.

^j^ISR: injection site reaction.

##### Randomized Injection Reminders via WhatsApp

As part of the consent process for enrollment in step 2, participants will be informed that they may be selected to receive a WhatsApp appointment reminder 2 days before each scheduled injection visit. Participants will be randomly assigned (1:1) to either the SOC (verbal communication and paper appointment slip letting participants know when they should come back to the clinic) or SOC plus WhatsApp arm using simple or block randomization and will be informed of which arm they are assigned to during the step 2 enrollment visit. During the month 5 visit, participants who were randomized to receive WhatsApp appointment reminders will be asked to complete a brief participant survey to assess the acceptability of receiving WhatsApp appointment reminders. If a participant does not return for their month 5 visit, the survey will be administered at their next clinic visit.

##### Switching From Oral TDF and FTC PrEP to CAB-LA PrEP

Step 1 participants may choose to switch from oral TDF and FTC PrEP to CAB-LA PrEP only once during the study period. These participants will undergo all step 2 procedures prior to receiving the first CAB-LA injection. Individuals with hepatitis B surface antigen–positive results and indication of hepatitis B treatment will be counseled to remain on oral TDF and FTC for PrEP. If hepatitis B treatment is not indicated and the individual chooses to switch to CAB-LA, enrollment will be allowed unless exclusionary hepatic criteria are identified (alanine aminotransferase ≥5 × upper limit of normal).

##### Specific Visit Procedures

Participants included in step 2 to receive CAB-LA PrEP who decide to discontinue participation before completing the minimum 1 year and maximum 2 years of study follow-up will complete early discontinuation visit procedures (Table 3). These participants will be invited to participate in a 12-month extension follow-up to safely monitor the CAB-LA “tail” phase and will be offered oral PrEP (TDF and FTC). Some of them will be invited to participate in a qualitative interview to describe their experience with CAB-LA PrEP and the reason for decision to discontinue CAB-LA PrEP.

If a participant misses an appointment but wishes to continue with CAB-LA PrEP, reloading with CAB-LA may be necessary, and the participant will need repeat HIV rapid tests before receiving a new CAB-LA injection. Oral bridging with TDF and FTC will be offered to participants who anticipate not being able to attend their scheduled injections (planned missed injections) in the +7 or −7-day window, starting approximately 2 months after the last injection dose of CAB-LA.

**Table 3 table3:** The ImPrEP CAB Brasil–specific visit procedures.

Procedures			Final visit		Early discontinuation^a^		Seroconversion		STI^b^ interim visit		AE^c^ interim visit
**Administrative, behavioral, and clinical**											
	HIV counseling	✓		✓		✓		✓			
	Reproductive counseling^d^	✓		✓		✓^e^		✓^e^		✓^e^	
	Condom, lubricant, and HIVST^f^	✓		✓		✓		✓			
	Adherence counseling	✓		✓		✓					
	HIV Risk and Mental health assessment	✓		✓		✓				✓	
	Medical history	✓		✓		✓		✓		✓	
	Concomitant medication	✓		✓		✓		✓		✓	
	Physical examination	✓		✓		✓		✓		✓	
	Weight and vital Signs	✓		✓		✓					
	Height	✓		✓		✓					
	HIVST report	✓		✓^g^		✓^g^		✓^g^		✓^g^	
**Laboratory**											
	Third-generation HIV rapid test	✓		✓		✓		✓			
	HIV RNA PCR^h^ (GeneXpert)	✓		✓				✓^i^			
	HIV RNA PCR					✓					
	HBV^j^ rapid test	✓		✓		✓		✓			
	HCV^k^ rapid test	✓		✓		✓		✓			
	Syphilis test	✓		✓		✓		✓			
	Liver function test (ALT^l^)	✓		✓		✓				✓^m^	
	Creatinine or ClCr^n^	✓^o^		✓^o^							
	Oropharyngeal CT^p^ and NG^q^ test	✓		✓		✓		✓			
	Urine CT and NG test	✓		✓		✓		✓			
	Rectal swab CT and NG test	✓		✓		✓		✓			
	Urine pregnancy test	✓^r^		✓^r^		✓^r^		✓^e^		✓^e^	
	CD4 cell count					✓					
	HIV resistance testing					✓					
	Plasma and serum storage	✓		✓		✓					
**Study medication**											
	Injection	✓^d^									
	ISR^s^ evaluation	✓^d^								✓^t^	
	ART^u^ initiation					✓					
	TDF^v^ and FTC^w^ PrEP^x^	✓^y^		✓^y^							

^a^Any discontinuation occurring before the anticipated final study visit and not related to seroconversion.

^b^STI: sexually transmitted infection.

^c^AE: adverse event.

^d^Depending on the scenario that presents itself at the time of the final study visit.

^e^If pregnancy is suspected.

^f^HIVST: HIV self-test.

^g^If available.

^h^PCR: polymerase chain reaction.

^i^If HIV infection is suspected.

^j^HBV: hepatitis B.

^k^HCV: hepatitis C.

^l^ALT: alanine aminotransferase.

^m^Interim visits performed because of suspected hepatic adverse events should collect liver function tests.

^n^ClCr: creatinine clearance.

^o^If oral preexposure prophylaxis is initiated.

^p^CT: *Chlamydia trachomatis.*

^q^NG: *Neisseria gonorrhea.*

^r^Only for transgender men.

^s^ISR: injection site reaction.

^t^Interim visits performed because injection site reactions should follow specific protocol instructions.

^u^ART: antiretroviral therapy.

^v^TDF: tenofovir disoproxil fumarate.

^w^FTC: emtricitabine.

^x^PrEP: preexposure prophylaxis.

^y^In a final study visit or an early discontinuation visit, if the participant chooses to switch to oral preexposure prophylaxis, they will be followed in the 12-month follow-up study.

#### Study Step 3

Participants from step 2 will be invited to participate in step 3 if they meet the following eligibility requirements: (1) the participant decides to switch from CAB-LA to oral TDF and FTC during study follow-up or (2) the participant decides to early discontinue CAB-LA injections but does not want to start oral PrEP.

Participants who choose to switch from CAB-LA to oral TDF and FTC will need to complete the procedures related to the daily oral TDF and FTC enrollment visit (Table 3). The procedures are the same as those specified under both the early discontinuation visit and the final study visit, plus creatinine dosage and estimated creatinine clearance. Once enrolled in step 3, the follow-up consists of visits scheduled for the following intervals: month 1, month 4, month 7, month 10, and month 13 or year 1 (Table 4).

Participants who choose to keep off PrEP will be invited to be followed up in step 3. Participants will have quarterly visits with sexual risk assessment, HIV and STI testing and counseling, and the provision of condoms and lubricants.

**Table 4 table4:** The ImPrEP CAB Brasil step 3 procedures: daily oral preexposure prophylaxis.

Procedures			Enrollment^a^		Month 1		Month 4		Month 7		Month 10		Month 13 or year 1
**Administrative, behavioral, and clinical**													
	Locator information	✓		✓		✓		✓		✓		✓	
	HIV risk assessment and counseling	✓		✓		✓		✓		✓		✓	
	Condom, lubricant, and HIVST^b^	✓		✓		✓		✓		✓		✓	
	Adherence counseling	✓		✓		✓		✓		✓		✓	
	Medical history	✓		✓		✓		✓		✓		✓	
	Concomitant medication	✓		✓		✓		✓		✓		✓	
	Directed physical examination	✓		✓		✓		✓		✓		✓	
	Weight and vital Signs	✓		✓		✓		✓		✓		✓	
	Height	✓										✓	
	HIVST report			✓		✓		✓		✓		✓	
**Laboratory**													
	Third-generation HIV rapid test	✓		✓		✓		✓		✓		✓	
	HBV^c^ rapid test	✓						✓				✓	
	HCV^d^ rapid test	✓						✓				✓	
	Syphilis test	✓				✓		✓		✓		✓	
	Liver function test (ALT^e^)^f^	✓						✓				✓	
	Creatinine or ClCr^g^	✓						✓				✓	
	Oropharyngeal CT^h^ and NG^i^ test	✓				✓		✓				✓	
	Urine CT and NG test	✓				✓		✓		✓			
	Rectal swab CT and NG	✓				✓		✓		✓			
	Plasma and serum storage	✓		✓		✓		✓		✓		✓	
**PrEP^j^ medication**													
	TDF^k^ and FTC^l^ dispensation	✓		✓		✓		✓		✓		✓	

^a^Enrollment procedures for oral preexposure prophylaxis are the same as those of the final study visit and early discontinuation visit.

^b^HIVST: HIV self-test.

^c^HBV: hepatitis B.

^d^HCV: hepatitis C.

^e^ALT: alanine aminotransferase.

^f^Only for those who switched from long-acting injectable cabotegravir.

^g^ClCr: creatinine clearance.

^h^CT: *Chlamydia trachomatis.*

^i^NG: *Neisseria gonorrhea*.

^j^PrEP: preexposure prophylaxis.

^k^TDF: tenofovir disoproxil fumarate.

^l^FTC: emtricitabine.

#### Step 4

##### Overview

Participants who are diagnosed with HIV while using CAB-LA during study follow-up will perform the procedures related to the *seroconversion visit* (Table 3) and will be invited to join step 4. HIV treatment will be initiated in accordance with the Brazilian guidelines. The participant will be requested to come to the study clinic for quarterly visits for 1 year. HIV RNA polymerase chain reaction will be evaluated in all visits. If a participant is identified with suspected virological failure, a new resistance test will be performed, and a new ART regimen will be selected based on the resistance test results.

##### Qualitative Assessments During the Study

At month 7, a select set of participants will be invited to participate in a semistructured qualitative interview guided by the TFA to understand their experiences with CAB-LA PrEP and with the clinic services, including WhatsApp appointment reminders and HIV self-testing. Up to 16 participants will be interviewed at each site. The aim is to sample approximately 8 individuals who continually adhered to their injection schedule, approximately 4 individuals who needed to reload, and 4 individuals who discontinued CAB-LA injections. Interviews will be conducted in Portuguese and audio recorded. Interviewers will complete a debriefing report summarizing the key points of the interview within 12 hours of completing the interview. Audio recordings will be transcribed *verbatim* by study staff.

##### Health Care Provider Survey

At the end of the implementation study, health providers will be asked to complete an in-depth interview on their experiences integrating CAB-LA in the existing PrEP services and their views on the mHealth tool and WhatsApp reminders. The interview questionnaire will seek to understand the facilitators of and barriers to CAB-LA service delivery and will be informed by implementation science constructs drawn from the TFA (affective attitude, burden, ethicality, intervention coherence, opportunity cost or relative advantage, perceived effectiveness, and self-efficacy) [29], Reach, Effectiveness, Adoption, Implementation, and Maintenance (implementation) [30], and Proctor et al [31] (feasibility). The definitions of the constructs are summarized in Multimedia Appendix 1. During these interviews, health care providers will also be asked to review their most recent process mapping, describe changes that happened with CAB-LA implementation, and describe ongoing “pain points." Short Likert-scale surveys will also be embedded in the questionnaires to gather quantitative data on acceptability.

### Major Outcomes

The major clinical and implementation outcomes, levels of analysis, methods, and timing are described in Table 5.

**Table 5 table5:** Summary of major clinical and implementation outcomes.

Major outcomes		Level	Methods and timing
**Clinical**			
	HIV incidence (effectiveness)	Individual	HIV test completed at each visit and interim analysis after 12 months of enrollment and upon the completion of the study
	Resistance to CAB-LA^a^ or oral TDF^b^ and FTC^c^ PrEP^d^ (effectiveness and safety)	Individual	HIV genotyping test at the time of seroconversion or suspected viral failure at any time during the 12-month follow-up

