**Methods:**

This type-2 hybrid implementation-effectiveness study includes formative work, qualitative assessments, and clinical steps 1 to 4. For formative work, we will use participatory design methods to develop an initial CAB-LA implementation package and process mapping at each site to facilitate optimal client flow. SGMs aged 18 to 30 years arriving at a study clinic interested in PrEP (naive) will be invited for step 1. Individuals who tested HIV negative will receive mHealth intervention and standard of care (SOC) counseling or SOC for PrEP choice (oral or CAB-LA). Participants interested in CAB-LA will be invited for step 2, and those with undetectable HIV viral load will receive same-day CAB-LA injection and will be randomized to receive digital appointment reminders or SOC. Clinical appointments and CAB-LA injection are scheduled after 1 month and every 2 months thereafter (25-month follow-up). Participants will be invited to a 1-year follow-up to step 3 if they decide to change to oral PrEP or discontinue CAB-LA and to step 4 if diagnosed with HIV during the study. Outcomes of interest include PrEP acceptability, choice, effectiveness, implementation, and feasibility. HIV incidence in the CAB-LA cohort (n=1200) will be compared with that in a similar oral PrEP cohort from the public health system. The effectiveness of the mHealth and digital interventions will be assessed using interrupted time series analysis and logistic mixed models, respectively.

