## Results

During the third and fourth quarters of 2022, we obtained regulatory approvals; programmed data entry or management systems; trained sites; and performed community consultancy, process mapping, and formative work. Study enrollment is anticipated to happen in the first quarter of 2023. The planned activities are presented in Table 7.

**Table 7 table7:** Planned activities for the ImPrEP CAB Brasil study (2022-2024).

Activities	Quarter 2 of 2022	Quarter 3 of 2022	Quarter 4 of 2022	Quarter 1 of 2023	Quarter 2 of 2023	Quarter 3 of 2023	Quarter 4 of 2023	Quarter 1 of 2024	Quarter 2 of 2024	Quarter 3 of 2024	Quarter 4 of 2024
Regulatory submission	✓										
Regulatory approvals		✓	✓								
Data entry or management systems programmed	✓	✓									
Drug importation and distribution				✓	✓						
Site equipping	✓	✓	✓								
SOP^a^ and SSP^b^ development	✓	✓	✓	✓							
Staff selection	✓	✓									
Staff training		✓	✓								
Process mapping			✓								
Formative work		✓	✓	✓							
Enrollment					✓	✓	✓				
Follow-up						✓	✓	✓	✓	✓	
Data consolidation							✓	✓	✓	✓	
Data analysis										✓	✓
Final report											✓
Manuscript submission											✓

^a^SOP: standard operational procedures.

^b^SSP: study-specific plan.

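### Table 7 ends follow-up in Q3 2024 and reports in Q4 2024, which leaves no room for the 12-month step 3 and step 4 windows, including the viral-failure part of the resistance outcome

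*Protocol article*

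**What the plan says.** All references are to the protocol article.

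- **Resistance outcome** (Major Outcomes, Table 5, Clinical): "HIV genotyping test at the time of seroconversion or suspected viral failure at any time during the 12-month follow-up".
- **Step 4** (Step 4, Overview): "The participant will be requested to come to the study clinic for quarterly visits for 1 year". Also: "If a participant is identified with suspected virological failure, a new resistance test will be performed".
- **Step 3, early discontinuers** (Specific Visit Procedures): they are invited to a "12-month extension follow-up to safely monitor the CAB-LA “tail” phase".
- **Step 3, final-visit switchers** (Table 3, note y): "if the participant chooses to switch to oral preexposure prophylaxis, they will be followed in the 12-month follow-up study".
- **Length of step 2**: Specific Visit Procedures describes early discontinuation as leaving "before completing the minimum 1 year and maximum 2 years of study follow-up". The Abstract and Table 2 give a schedule of 25 months. Statistical Analysis assumes an average of 1.5 years.
- **Calendar** (Results, Table 7, covering 2022 to 2024): enrollment in Q2-Q4 2023; a single follow-up row from Q3 2023 to Q3 2024 that names no step; data analysis in Q3-Q4 2024; final report and manuscript in Q4 2024. No follow-up is marked after Q3 2024.

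**The concern.** The step 3 and step 4 windows open when a participant leaves CAB-LA or is diagnosed. That can be as late as the last step 2 visit, and each window then runs for a year. Study Design also lets a participant diagnosed during step 3 enter step 4, so one window can follow another. Table 7 sets aside no time for this.

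If the Q4 2024 report is treated as final, resistance at later viral failure and the step 4 ART results would rest largely on incomplete windows. Failures that occur after the cut would not be counted. The 12-month monitoring after CAB-LA would contain no complete record from anyone who entered it at the final visit. With 8 to 18 seroconversions illustrated in Table 6, a few unfinished windows are a large share of the information.

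**Working it through.** **The plan's own figure.** Statistical Analysis gives 1350 person-years: 1200 × 1.5 × 0.75 = 1350, which reproduces. The article gives no figure for completed step 3 or step 4 follow-up, so that has to be derived.

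**Set-up.** Count months from 1 April 2023. Table 7 then puts enrollment at months 0-9, the end of follow-up at month 18 (30 September 2024) and the end of the report quarter at month 21 (31 December 2024). Assumptions not in the article: uniform enrollment, constant hazard of diagnosis, and either no loss or exponential loss at 75% retention a year.

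Under a constant hazard, the share of seroconverters with a full 12 months is

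person-time accrued up to (closing date − 12 months) ÷ total step 2 person-time.

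**Seroconverters on Table 7's dates, no loss**

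- Total step 2 person-time per enrollee: mean of (18 − u) for u uniform on 0-9 = 18 − 4.5 = 13.5 months.
- Step 4 closes at month 18, so diagnosis is needed by month 6. Mean of (6 − u), zero after month 6, = (6²/2)/9 = 2.0 months. Share = 2.0/13.5 = 14.8%.
- Step 2 stops at month 18 and step 4 alone runs to month 21, so diagnosis is needed by month 9. Mean of (9 − u) = 4.5 months. Share = 4.5/13.5 = 33.3%.

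With 75% annual retention the two shares are 1.91/11.47 = 16.6% and 4.19/11.47 = 36.5%.

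Applied to Table 6's 8, 12 or 18 CAB-LA cases, 14.8% is 1.2, 1.8 or 2.7 cases with a complete step 4 window.

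**Sensitivity to the start date.** The Results text anticipates enrollment in Q1 2023, while the Abstract and Table 7 say Q2. Spreading enrollment over all of 2023 and counting from January, total person-time is 21 − 6 = 15 months. Closing in Q3 2024 gives (9²/2)/12 = 3.375, and 3.375/15 = 22.5%. Running step 4 alone to the end of Q4 gives 6/15 = 40%.

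**Final-visit switchers.** No distributional assumption is needed. First enrollment in April 2023 + 1-year minimum + 12 months = April 2025, after the Q4 2024 report. The earliest such switch (April 2024) leaves at most 6 months to the end of September 2024 and 9 to the end of December. A January 2023 start gives January 2025, still too late.

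**If the step 2 calendar is repaired.** Table 7 allows step 2 only 9 months (last enrolled) to 18 months (first enrolled), an average of 13.5 against the stated 1.5 years. It would therefore have to be lengthened in any case. The seroconverter share then depends on how:

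| Repair of step 2 | Diagnosis needed by | Share complete, no loss | With 75% annual retention |
|---|---|---|---|
| 12-24 months each: 12-month accrual, common close at month 24 | month 12 | 6/18 = 33% | 38% |
| 25 months each: 9-month accrual, close at last visit (month 34) | month 22 | 17.5/25 = 70% | 76% |

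In both rows, a participant who switches at the last step 2 visit has no post-CAB-LA follow-up at close. In the first row every final visit falls at month 24. In the second, final visits fall at months 25-34, leaving at most 9 months. No final-visit switcher reaches 12 months in either.

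**The case against.** - **The resistance outcome does not as a whole need 12 months.** This is right. The genotype at seroconversion needs no later follow-up, and Table 3 places resistance testing at the seroconversion visit. A reader might infer that the whole resistance outcome is cut off; the article does not support that. Partial step 4 follow-up also contributes, because HIV RNA is measured at every quarterly visit. How many later failures would be missed cannot be computed from the article.
- **A reader might infer that most seroconverters are cut off however step 2 is repaired.** That is not supported. It holds on Table 7's dates and with 12-24 months of step 2 and a common close. It reverses to about 70% complete if everyone follows the 25-month schedule and the study closes at the last visit. Much of the seroconverter shortfall comes from Table 7 being too short for step 2 itself.
- **Table 7 does not say that its follow-up row is step 2.** Correct. The conflict does not turn on this: if the row covers all steps, they all stop in Q3 2024; if it covers step 2 only, steps 3 and 4 have no row.
- **Tail incidence is not a Table 5 outcome.** Also correct. Specific Visit Procedures describes the tail follow-up as safety monitoring, so what is truncated is monitoring, not a named major outcome.
- **A later report may be planned in the full protocol or SAP.** Possible, and the wording of Table 3, note y could point to a separate extension study. The point does not depend on that silence: the published calendar gives dates that its own 12-month windows do not fit.

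**Conclusion.** The point holds as an internal inconsistency between Table 7 and the 12-month windows in Table 5, Specific Visit Procedures, Table 3 (note y) and Step 4.

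- On Table 7's dates, about 15-17% of seroconverters can complete step 4 by the end of Q3 2024, and about 33-37% if step 4 alone runs to the end of Q4. These shares assume uniform enrollment over Q2-Q4 2023 and a constant hazard.
- No final-visit switcher can complete 12 months before the report. This rests only on the stated dates and the 1-year minimum.
- The affected results are resistance at later viral failure, step 4 ART monitoring and tail monitoring. The seroconversion genotype is not affected, and the HIV-incidence analysis does not depend on these windows.
- Once step 2 is repaired, the seroconverter share may be anywhere from about 33% to 70% without loss. Final-visit switchers are cut off under any repair that stops at step 2 close.

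This should be corrected, but it is a matter of calendar and reporting, not a flaw in the outcome definition.

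**What to change.** Reconcile Table 7 with Table 5, Specific Visit Procedures, Table 3 (note y) and Step 4:

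1. Label the follow-up row by step, and add step 3 and step 4 rows running 12 months past the last step 2 visit. State how a diagnosis made during step 3 is handled, since Study Design lets it open a further year.
2. At the step 2 lock, report HIV incidence and resistance from the seroconversion genotype.
3. Report resistance at viral failure, ART outcome and step 3 results at a second, later lock.
4. Label any earlier report of these as interim, and give the number of participants with a complete 12-month window.

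The cost is a second lock and a supplementary report about 12 months after the first. The visits are already in the protocol, so no procedures or participants are added and the incidence report is not delayed. The downside is a later final result for the step 3 and step 4 outcomes.
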